# A multicenter prospective cohort study to evaluate feasibility of radio-frequency identification surgical guidance for nonpalpable breast lesions: design and rationale of the RFID Localizer 1 Trial

**DOI:** 10.1186/s12885-022-09394-7

**Published:** 2022-03-22

**Keywords:** Breast cancer, Localization, Breast conserving surgery, Radiofrequency identification, RFID

## Abstract

**Background:**

Breast cancer screening and improving imaging techniques have led to an increase in the detection rate of early, nonpalpable breast cancers. For early breast cancer, breast conserving surgery is an effective and safe treatment. Accurate intraoperative lesion localization during breast conserving surgery is essential for adequate surgical margins while sparing surrounding healthy tissue to achieve optimal cosmesis. Preoperative wire localization and radioactive seed localization are accepted standard methods to guide surgical excision of nonpalpable breast lesions. However, these techniques present significant limitations. Radiofrequency identification (RFID) technology offers a new, nonradioactive method for localizing nonpalpable breast lesions in patients undergoing breast conserving surgery. This study aims to evaluate the feasibility of RFID surgical guidance for nonpalpable breast lesions.

**Methods:**

This multicenter prospective cohort study was approved by the Institutional Review Board of the University Medical Center Utrecht. Written informed consent is obtained from all participants. Women with nonpalpable, histologically proven in situ or invasive breast cancer, who can undergo breast conserving surgery with RFID localization are considered eligible for participation. An RFID tag is placed under ultrasound guidance, up to 30 days preoperatively. The surgeon localizes the RFID tag with a radiofrequency reader that provides audible and visual real-time surgical guidance.

The primary study outcome is the percentage of irradical excisions and reexcision rate, which will be compared to standards of the National Breast Cancer Organisation Netherlands (NABON)(≤ 15% irradical excisions of invasive carcinomas). Secondary outcomes include user acceptability/experiences, learning curve, duration and ease of the placement- and surgical procedure and adverse events.

**Discussion:**

This study evaluates the feasibility of RFID surgical guidance for nonpalpable breast lesions. Results may have implications for the future localization techniques in women with nonpalpable breast cancer undergoing breast conserving surgery.

**Trial registration:**

Netherlands National Trial Register, NL8019, registered on September 12^th^ 2019.

**Supplementary Information:**

The online version contains supplementary material available at 10.1186/s12885-022-09394-7.

## Background

Breast cancer screening and improving imaging techniques lead to an increase in the detection rate of early, nonpalpable breast cancers [1]. For early breast cancer, breast conserving surgery is an effective and safe treatment [2]. Accurate intraoperative lesion localization during breast conserving surgery is essential for adequate surgical margins while sparing surrounding healthy tissue to achieve optimal cosmesis.

Various lesion localization methods are currently used. Preoperative wire placement under image guidance was first described in 1965 by Dodd and has been the standard localization method since [3–5]. This technique requires careful logistical planning as the wire needs to be placed on the day of surgery, which can lead to significant workflow inefficiencies and operative delays. Furthermore, there is little time left for the surgeon to evaluate the imaging after wire placement and to communicate with the radiologist. The wire entry site may differ from the ideal surgical approach. Other disadvantages of wire localization are the risk of migration or dislodgement and patient anxiety caused by the wire protruding from the patient’s skin.

Radioactive I-125 seed localization was designed to overcome these limitations and has shown non-inferiority to wire localization in surgical outcomes including surgical margins, reexcision and reoperation rates, specimen size and cosmetic result [4, 6, 7]. However, the use of radioactive seeds is constrained by stringent nuclear regulatory issues. Obtaining and maintaining proper licensing and meticulous tracking of the radioactive seed is mandatory. These regulatory disadvantages have limited the widespread adoption of this technique and have prompted research and development of nonradioactive, non-wire localization methods [8–10].

Radiofrequency identification (RFID) technology may offer an alternative method for localizing nonpalpable breast lesion in patients undergoing breast surgery. The RFID system consists of a RFID tag and a handheld reader. The RFID tag contains a microchip with a unique identification number and an antenna that responds to the radiofrequency signal send by the reader. The tag alters and reemits the signal to the reader, which responds with an audio signal and displays the tag’s unique identification number and the distance to the nearest end of the tag. The audible and visual feedback provide the surgeon with real-time guidance during the excision procedure.

Although data on the use of RFID localization is limited, resulting from a proof-of-concept study [11], some small, single-center cohort studies [12–15], and one retrospective cohort analysis [16], all authors conclude that RFID tags are safe and effective in localizing nonpalpable breast lesions. Further clinical research in a prospective multicenter cohort is necessary to substantiate these first reports. Therefore, the RFID Localizer 1 Trial aims to evaluate the feasibility of RFID surgical guidance for nonpalpable breast lesions in a prospective multicenter cohort study.

## Methods and analysis

### Study design and setting

This prospective multicenter cohort study was designed to evaluate feasibility of RFID surgical guidance for nonpalpable breast lesions in two non-academic hospitals that acted as early adopters of RFID localization. The standard localization technique was wire-localizaton in one hospital and radioactive I-125 seed localization in the other. The primary study outcome is the percentage of irradical excisions and reexcision rate. Secondary outcomes include user acceptability/experiences, learning curve, duration and ease of the placement- and surgical procedure and adverse events.

### Study population and recruitment

Women, ≥ 18 years of age, with nonpalpable, histologically proven in situ or invasive breast cancer, who can undergo breast conserving surgery with RFID localization are considered eligible for participation (Table 1). All cancer subtypes may be included, provided that the lesion is visible on ultrasound imaging to enable RFID placement procedure under ultrasound guidance. Women with a lesion located deeper than 7 cm from the skin when lying supine cannot undergo RFID localization due to the maximum reach of the RFID reader of 7 cm. Women who are pregnant or lactating, women with multicentric breast cancer and women who are unable to understand and sign the study specific informed consent form after the nature of the study has been fully explained are excluded.

**Table 1 Tab1:** RFID Localizer 1 Trial patient eligibility

**Inclusion criteria**
Female patient ≥ 18 years of age Patient has a nonpalpable histologically proven in situ or invasive breast cancer that is visible on ultrasound Patient is scheduled for breast conserving surgery
**Exclusion criteria**
Lesion depth > 7 cm in supine position Patient has multicentric breast cancer Patient is pregnant or lactating Patient is unable to understand and sign the study specific informed consent form after the nature of the study has been fully explained *Patient will undergo neoadjuvant treatment*^a^

^a^Participating centers with access to I-125 seed localization will not include patients undergoing neoadjuvant treatment because in these patients a single procedure using I-125 seed is preferred over two procedures (using a marker followed by RFID tag placement)

In participating centers with access to I-125 seed localization, patients undergoing neoadjuvant treatment will be excluded because in these patients a single procedure using I-125 seed is preferred over two procedures (using a marker during neoadjuvant treatment followed by preoperative RFID tag placement). Study participants are recruited from the surgical outpatient clinic of the participating hospitals. Eligibility criteria are assessed during multidisciplinary meetings. Patient characteristics, including breast cup size, are recorded. Written informed consent is obtained from all study participants.

### Study procedures (Fig. 1)

**Fig. 1 Fig1:**
[figure not shown]
Overview of procedures and data collection of the RFID Localizer 1 Trial

Preoperative placement of an RFID tag is performed by an experienced breast radiologist, using ultrasound guidance, up to 30 days prior to surgery. The passive RFID tag is composed of a coil and a microchip that stores a unique identification number. The RFID tag is approximately 11 mm long and 2 mm in diameter. A polypropylene cap prevents migration in tissue. The RFID tag is inserted percutaneously through a small skin incision with a preloaded 12-gauge sterile needle applicator after injection of a local anaesthetic (lidocaine 2%). In tumors > 1 cm the RFID tag is placed intralesional, in lesions ≤ 1 cm the RFID tag is placed directly next to the tumor. The VAS pain score of the patient is recorded. A 2-view mammography (CC and MLO) is obtained to confirm correct position of the RFID tag. Successful placement is recorded, which is defined as 0-5 mm distance between any point of the tag to any point of the tumor measured on the post-placement imaging. Directly after the placement procedure the radiologist completes a questionnaire on the duration and ease of the procedure (Table 2).

**Table 2 Tab2:** Questionnaires

Respondents specify their level of agreement or disagreement for the following statements on the five-level Likert scale: Strongly disagree, Disagree, Neither agree nor disagree, Agree, Strongly agree
**Radiologists**
The RFID tag applicator is easy to handle The RFID tag applicator needle is sharp enough to penetrate healthy breast tissue The RFID tag applicator needle is sharp enough to penetrate tumor tissue RFID tag deployment is simple The RFID tag is clearly visible on ultrasound I feel confident about the correct placement of the RFID tag
**Surgeons**
The RFID tag is easily identified pre-operatively using the loop probe The RFID tag is easily identified during surgery I feel confident that the RFID technology leads me to the correct location The RFID localization procedure is intuitive to use

All surgical procedures are performed by an experienced oncology breast surgeon or an experienced surgical resident under direct supervision. At breast conserving surgery the surgeon localizes the RFID tag using the handheld, portable, battery-operated reader device (Fig. 2). The reader is bagged in a sterile drape for use in the sterile field. The reader has a loop probe with a detection range of up to 7 cm, and an attachable single-use sterile pencil probe (8 mm tip diameter) with a detection range up to 3.5 cm, intended for highly specific localization. The reader provides an audible signal that increases in pitch and volume when the probe is moved closer to the RFID tag. The reader also displays the distance from the probe to the tag in millimeters and the unique identification number of the RFID tag. The audible and visual feedback provide precise, real-time guidance during the excision procedure. Specimen radiography is performed to confirm successful retrieval of the RFID tag. Directly following the surgical procedure the surgeon completes a questionnaire on the duration and ease of the procedure.

**Fig. 2 Fig2:**
[figure not shown]
RFID LOCalizer system (Hologic). The RFID LOCalizer system (Hologic) consists of a preloaded 12-gauge sterile needle applicator (**A**) containing the RFID tag (**B**), a handheld, portable, battery-operated reader device (**C**) with a loop probe with a detection up to 7 cm of depth (**D**), and an attachable sterile pencil probe with a detection range up to 3.5 cm (**E**)

Histopathological analysis is performed following routine standard of care, including assessment of surgical margins. Surgical margins are classified as radical, focally irradical and irradical according to the Dutch breast cancer guideline [17] (Fig. 3). Irradical excision and indication for reexcision is recorded.

**Fig. 3 Fig3:**

Classification of surgical margins [17]. Radical excision is defined as no tumor at inked cut edges in an adequately processed specimen. Focally irradical excision is defined as one limited area (≤ 4 mm) of tumor (invasive carcinoma and/or DCIS) at inked cut edges. Irradical excision is defined as a larger area (> 4 mm) of tumor or multiple areas of tumor at inked cut edges [17]

Any adverse events potentially related to the RFID localization procedure, noted by the involved study radiologist, surgeon, pathologist, or other health care providers, are recorded. Post-operative wound infections, noted during post-operative follow-up visits as usual, are collected from the medical records 30 days after surgery by a study team member.

After completion of inclusion all users of the RFID localization system are invited to complete a questionnaire on system usability using the validated 10-item System Usability Scale [18]. All data is collected using Castor Electronic Data Capture.

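### Adverse events between tag placement and surgery may be under-recorded: they depend on a provider noting them as potentially related, and the one dated record search covers only post-operative wound infection

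*Protocol article*

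**What the plan says.** Under Study design and setting, the Protocol article places adverse events among the secondary outcomes: "Secondary outcomes include user acceptability/experiences, learning curve, duration and ease of the placement- and surgical procedure and adverse events".

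Under Study procedures it fixes the exposure: "Preoperative placement of an RFID tag is performed by an experienced breast radiologist, using ultrasound guidance, up to 30 days prior to surgery". The tag goes in through a small skin incision with a 12-gauge applicator.

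The paragraph after the margin classification (Fig. 3) states how safety data are collected. The general rule is "Any adverse events potentially related to the RFID localization procedure, noted by the involved study radiologist, surgeon, pathologist, or other health care providers, are recorded". One event has its own step: "Post-operative wound infections, noted during post-operative follow-up visits as usual, are collected from the medical records 30 days after surgery", a task given to a member of the study team.

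Three further observations are made in every patient: a VAS pain score and a two-view mammogram at placement, and specimen radiography at surgery to confirm that the tag was retrieved.

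**The concern.** Under the general rule an event reaches the data only if a health care provider notes it and regards it as potentially related to the localization procedure. For wound infection after surgery there is a second route: someone opens the record at a set time and looks. No such route is described for the interval between placement and surgery, although that interval starts with a skin incision and can last 30 days.

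The Background says that a wire must be placed on the day of surgery, and wire was the standard technique in one of the two hospitals. For that hospital the waiting interval with the tag in place is new.

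The article presents this cohort as the study needed to substantiate earlier small reports that the tags are safe and effective. A low or zero count for the pre-surgical interval would be read as support for that, yet it would partly reflect how events were sought.

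**Working it through.** **Reproducible figure.** The article gives no adverse event rate, expected rate, denominator or benchmark, so there is no stated figure to reproduce. The check is a comparison of what is looked for, when and how.

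| Observation | Interval covered | Route into the data |
|---|---|---|
| VAS pain score | Placement | Recorded in every patient |
| Two-view mammogram, tag position | Directly after placement | Obtained in every patient |
| Haematoma, insertion-site infection, later pain, unplanned contact | Placement to surgery (up to 30 days) | General rule only: noted by a provider and potentially related |
| Specimen radiography, tag retrieval | Surgery | Performed in every patient |
| Post-operative wound infection | Surgery to day 30 | Chart review at day 30 of what usual visits noted |
| Other post-operative events | After surgery | General rule only |

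The third row is the gap. The universal checks at either end show placement pain, tag position and tag retrieval. None is described as a search for a haematoma or infection arising in between. Surgery does bring every patient back to a provider, but the surgeon questionnaire items in Table 2 concern finding the tag, confidence and ease of use. None asks about adverse events.

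**Direction.** If *p* is the true rate and *s* the share that reaches the data, the expected observed rate is *p* × *s*. With *s* below 1 the observed rate is too low.

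**Size.** Neither *p* nor *s* is in the document. The values below are assumptions, with *N* = 200 from Sample size considerations.

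| Assumed *p* | *s* = 50% | *s* = 70% | *s* = 90% | Full capture |
|---|---|---|---|---|
| 2% | 1.0% (2.0 events) | 1.4% (2.8) | 1.8% (3.6) | 4.0 events |
| 5% | 2.5% (5 events) | 3.5% (7) | 4.5% (9) | 10 events |

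**A zero count.** The exact two-sided 95% upper limit for 0 of 200 is 1 − 0.025^(1/200) = 1.8%. The chance of recording no event is (1 − *p* × *s*)^200:

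- *p* = 1%, full capture: 0.99^200 = 0.13; half capture: 0.995^200 = 0.37.
- *p* = 2%, full capture: 0.98^200 = 0.02; half capture: 0.99^200 = 0.13.

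Incomplete capture therefore makes a reassuring zero more likely, but how much more depends entirely on the assumed *s*.

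**The case against.** The strongest reply is that this is a condensed article. Event lists, recording windows and causality fields commonly sit in the full protocol, and the figure that gives an overview of data collection is not shown. That stands in part: a search of the pre-surgical interval may exist elsewhere, and its absence here is not evidence that there is none. But the article does not leave the subject to another document. It states which events qualify, who notes them, which are retrieved from records and when. The relatedness condition and the limit of the dated review to wound infection are written rules.

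Several stronger readings are tempting, and the document does not support them.

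- *The pre-surgical interval is outside safety collection.* It is not. The general rule has no time limit, and its reporters include the pathologist and other health care providers as well as those using the device. Potential relatedness is also a wide threshold; an insertion-site haematoma should meet it once noted.
- *Wound infection is actively collected and nothing else is.* The day-30 step reads what usual visits happened to note, so it too depends on providers. The pain score, mammogram and specimen radiograph are made in every patient.
- *Half of the time at risk is unobserved.* The fraction 30/(30 + 30) = 50% applies only to a tag placed at the 30-day maximum, and that period includes the placement-day checks.
- *The adverse event rate is biased low.* This would need a true rate and a capture share. Any numerical example returns the share it assumed.
- *The relatedness filter can never be undone.* Events in the medical record can still be found there. Those excluded from the study data are lost only if nobody looks.

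The contrast with same-day wire also has limits. The other hospital used I-125 seeds, which the eligibility footnote describes as a single procedure for patients having neoadjuvant treatment, so a pre-surgical interval is not new there. The study is single-arm and claims no safety comparison.

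**Conclusion.** The point holds as a risk of under-recording, not as a demonstrated bias. The document describes a dated record search for one post-operative event and none for events between placement and surgery. Haematoma, insertion-site infection or unplanned contact in that interval may therefore be missed. The direction would be downward and the size cannot be computed; the figures above rest on assumed rates and capture shares. The conclusion also assumes that no unseen document adds a search of this interval.

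Only a secondary outcome is affected. The irradical excision and reexcision rates, and the sample size reasoning built on them, are unaffected. This is a cheap improvement, not a flaw that threatens the trial.

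**What to change.** In the Study procedures paragraph on adverse events:

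1. Start the existing day-30 chart review at the tag placement date.
2. Apply one short fixed list to both intervals, for example haematoma or bleeding, infection at the insertion site or wound, pain leading to unplanned contact, other unplanned visit or treatment, and tag displacement or loss.
3. Record every listed event whatever its suspected cause, and hold relatedness as a separate field completed afterwards.
4. Report counts from placement to surgery and from surgery to day 30 separately, over all women with a tag placement attempt.

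The same team member reads the same record over a longer interval, so no visit or procedure is added. The cost is a few more case record fields, more unrelated events in the listing, and a somewhat less favourable reported rate. The review would still find only what the records contain, so it reduces under-recording without removing it.

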### Statistical analysis

Data will be analyzed using SPSS and RStudio. Descriptive statistical analysis will include the calculation of means, medians and interquartile ranges of the obtained data. The percentage of irradical excisions will be calculated by dividing the number of irradical excisions by the total number of excisions, with the corresponding 95% confidence interval (CI). The reexcision rate will be calculated by dividing the total number of reexcisions by the total number of excisions, with the corresponding 95% CI. Questionnaire data is evaluated using the five-level Likert scale.

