### Sample size considerations

We aim to include a minimum of 200 patients over a study period of one year. This sample size is based on the primary study outcome of the percentage of irradical excisions and reexcision rate, which will be compared to standards of the National Breast Cancer Organisation Netherlands (NABON). The NABON standards set a maximum of irradical excisions of invasive carcinomas at 15% [19]. Based on earlier data we expect that with a study population of 200 women, approximately 174 will have invasive breast cancer [19]. To show that with RFID surgical guidance the upper boundary of the 95% CI of the percentage of radical excisions does not exceed the NABON standard of 15%, with 174 cases of invasive breast cancer, a maximum percentage of irradical excisions of 9% in our study population is needed. Therefore, a sample size of 200 women is considered feasible and sufficient to show a statistically and clinically relevant outcome.

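### The primary percentage of irradical excisions is defined over all excisions, but the 15% standard and the precision argument cover invasive carcinomas only

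*Protocol article*

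**What the plan says.** Four statements in the protocol article bear on this.

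- **Who is enrolled** (Study population and recruitment): women with "nonpalpable, histologically proven in situ or invasive breast cancer".
- **How the primary figure is computed** (Statistical analysis): "The percentage of irradical excisions will be calculated by dividing the number of irradical excisions by the total number of excisions", with a 95% confidence interval. The section mentions no restriction to invasive cases.
- **What it is compared with**: the abstract's Methods gives the standard as "≤ 15% irradical excisions of invasive carcinomas". Sample size considerations repeats it: "The NABON standards set a maximum of irradical excisions of invasive carcinomas at 15" percent. Both places say that the primary outcome will be compared with the NABON standards.
- **What the sample size rests on** (Sample size considerations): "Based on earlier data we expect that with a study population of 200 women, approximately 174 will have invasive breast cancer". The aim is that "the upper boundary of the 95% CI of the percentage of radical excisions does not exceed the NABON standard of 15" percent, where "radical" is evidently a slip for irradical. With 174 invasive cases, the section says that the observed percentage may be at most 9%, but it attaches that ceiling to the study population rather than to the invasive cases.

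**The concern.** The analysis section fixes one denominator and the sample-size section argues from another, and nothing reconciles them. An analyst who follows the analysis section literally puts about 200 excisions in the denominator and sets the result against a limit that does not cover the in situ part. An analyst who follows the sample-size section uses about 174. Both could say that they followed the protocol, so the choice could be made after the results are known.

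This is the primary outcome and the article's only numerical criterion. If the pooled figure is held to 15%, the conclusion depends partly on the in situ margin rate. A high in situ rate can fail a technique that meets the invasive standard. A low one can pass a technique that does not.

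**Working it through.** **Inputs.** From Sample size considerations: 200 women, 174 expected invasive, limit 15%, ceiling 9%. By subtraction, 200 − 174 = 26 in situ. Assumptions: one excision per woman, a two-sided 95% interval, and a pass when the upper limit is at most 15%. The article names no interval method and gives no in situ irradical rate.

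**Formulas** for x irradical among n, with p = x/n and z = 1.96:
- Exact (Clopper-Pearson) upper limit: the 0.975 quantile of Beta(x + 1, n − x).
- Wilson upper limit: [p + z²/(2n) + z√(p(1 − p)/n + z²/(4n²))] / (1 + z²/n).
- Agresti-Coull upper limit: p̃ + z√(p̃(1 − p̃)/ñ), with ñ = n + z² and p̃ = (x + z²/2)/ñ.

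**Step 1: reproduce the article's 9%.** At n = 174, all three methods give 16 as the largest passing count: 16/174 = 9.2%, with upper limits of 14.5% (exact), 14.4% (Wilson) and 14.5% (Agresti-Coull). At 17/174 they are 15.2%, 15.1% and 15.2%. The 9% is therefore right on the invasive-only denominator. At n = 200 the largest passing count is 19 by exact limits (9.5%, upper limit 14.4%) and 20 by Wilson (10.0%, upper limit 14.9%). That is a different rule for a different population.

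**Step 2: can the two denominators disagree?** The in situ counts below are illustrative.

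| Invasive | Exact upper limit | In situ | All excisions | Exact upper limit |
|---|---|---|---|---|
| 17/174 = 9.8% | 15.2%, fails | 1/26 | 18/200 = 9.0% | 13.9%, passes |
| 16/174 = 9.2% | 14.5%, passes | 5/26 | 21/200 = 10.5% | 15.6%, fails |

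Wilson and Agresti-Coull limits give the same four verdicts.

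**Step 3: how far does pooling move the percentage?** The pooled rate is (174 × invasive rate + 26 × in situ rate)/200. With an invasive rate of 9%:
- in situ rate 5%: (15.66 + 1.30)/200 = 8.5%;
- in situ rate 40%: (15.66 + 10.40)/200 = 13.0%.

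**Step 4: chance of passing**, using the exact cut-offs. Invasive-only: P[Bin(174, invasive rate) ≤ 16]. Pooled: P[Bin(174, invasive rate) + Bin(26, in situ rate) ≤ 19].

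| True invasive rate | Invasive-only | Pooled, by assumed in situ rate |
|---|---|---|
| 7% | 90% | 90% (at 10%), 82% (at 15%), 71% (at 20%), 46% (at 30%) |
| 15% | 1.6% | 4.6% (at 5%), 2.7% (at 10%), 1.5% (at 15%) |

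The second row is the chance of passing when the true invasive rate only just equals the limit.

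**The case against.** The best defence is that the article, read as a whole, already points to the right comparison. Both statements of the standard say invasive, and the interval argument is made on 174 invasive cases. The analysis section gives general formulas for two rates and mentions neither NABON nor 15%, so its denominator could be read as all excisions in whichever group is reported. The article is also a condensed account, and the full protocol may define the subset.

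Much of this stands, and it limits the point. A reader might infer that the study cannot be tested against its benchmark, or that the investigators will hold the pooled figure to 15%. The article supports neither. The invasive-only percentage can be derived from the routine histopathology, and no sentence explicitly sets a pooled interval against the limit. It does not remove the mismatch, however. The analysis section states a denominator instead of leaving it open, the primary outcome is said to be compared with NABON, and the 9% ceiling is attached to the whole study population.

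The size is also open to challenge. At in situ rates of about 7% to 15%, pooling changes the chance of passing only modestly. The larger losses need rates of 20% or more, and a raised false-pass chance needs in situ margins clearly better than invasive ones; the article gives no evidence for either. The reversals are not universal across methods: a simple Wald interval passes all four counts in Step 2, and a Jeffreys interval passes 17/174 (14.8%). Those two methods, however, allow 18/174 (10.3%) and 17/174 (9.8%), so neither reproduces the stated 9%.

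Finally, an all-excision rate is a legitimate description in a feasibility cohort of both histologies. The objection is only to holding it to 15%.

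**Conclusion.** The point holds as a mismatch between a stated formula and its own benchmark. The sample-size arithmetic is sound; the denominator in Statistical analysis is what needs correcting.

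Near the threshold, the two denominators can give opposite conclusions in either direction under the exact, Wilson and Agresti-Coull methods. The expected effect ranges from negligible to a fall in the chance of passing from 90% to 46%, at a true invasive rate of 7% and assumed in situ rates from 10% to 30%. These figures rest on the expected 174/26 split, one excision per woman and exact limits. Because the in situ rate is unknown, the range should be quoted and not one value from it. The mismatch affects the primary conclusion and is cheap to repair, so it should be settled before the outcome data are analysed.

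**What to change.** 1. In Statistical analysis, state that the NABON comparison uses irradical excisions among patients with invasive carcinoma, divided by all excisions in patients with invasive carcinoma, with its 95% confidence interval and the upper limit compared with 15%. Naming the interval method in the same sentence would help, since 17/174 passes or fails depending on it.
2. Report the all-excision and in situ percentages separately, each with its interval and without comparison to 15%.
3. In Sample size considerations, attach the 9% ceiling to the invasive cases.

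The cost is a few sentences, with no new data and no extra patients. The interval used for the comparison rests on about 174 cases instead of 200, which the sample-size section already assumes.
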